## Abstract

Low levels of physical activity (PA) are a concern among students, producing negative physical, health and mental consequences. This study aims to present a protocol intervention in physical education (PE) based on self-determination theory (SDT) to enhance students’ motivation towards performing PA and increasing their PA levels in their leisure time. This protocol is a convenience study with two allocation arms (intervention group versus control group). SDT-based motivational strategies will be carried out and co-created with PE teachers to increase motivation and out-of-school PA levels. Data collection will be conducted three times: before the intervention, after the intervention (four months after baseline) and at the end of the intervention (retention measurement, seven months after baseline). The measures will assess perceived teacher support for PA, motivation towards PA, intention to be physically active, PA levels, engagement in PE and academic performance. Overall, this intervention programme is expected to increase students’ autonomous motivation for PA and their PA levels in their free time. This intervention might encourage teachers to establish strategies and resources to increase their students’ adaptive outcomes.

## 1. Introduction

Regular physical activity (PA) has been associated with many physical, psychological, social, and cognitive benefits [1,2,3,4]. To achieve these benefits, the World Health Organization recommends that children and adolescents aged 5–17 years engage in at least 60 min of moderate-to-vigorous intensity PA (MVPA) per day [1]. Despite these benefits, the latest report on global PA trends, which included 1.6 million students worldwide from 146 different countries, found that more than 81% of 11–17-year-olds do not meet the daily PA recommendations [5]. Likewise, the Global Matrix 4.0 report for PA in 57 countries highlighted that, at the European level, only 34–39% met the PA recommendations [6].

Since school is the place where students expend most of their time, this context is crucial to explain and encourage specific behaviours (e.g., cognitive and academic development, development at behavioural, cellular, functional and morphological levels) [4]. Although the educational context is a favourable environment to generate healthy behaviours such as PA, the fact is that boys and girls spend a lot of time seated [7]. It has been shown that there is a need to develop strategies to encourage PA practice in students as PE levels during school hours are not enough [7]. In this sense, motivation is a fundamental variable to understand, explain, and improve positive consequences in and out of the classroom. Nevertheless, to identify the motivational parameters of students’ motivation for PA, we must determine the reasons for practising PA [8]. Previous research has shown that school interventions based on behaviour change theories (e.g., self-determination theory [SDT], goal perspectives theory, social cognitive theory) are more effective in promoting PA [9]. Therefore, considering the few existing studies that have promoted in-school and out-of-school PA, more intervention studies are needed to promote motivation and adherence towards PA and alleviate dropout from PA over time [7].

### 1.1. Physical Activity and Self-Determination Theory

Motivation has emerged as a crucial antecedent of students’ development and learning in the school context [10]. For this reason, SDT [8,11] has been widely used to promote motivation for PA and PA levels in students. As defined in SDT, motivation fluctuates seamlessly between higher and lower levels of self-determination, which refers to the extent to which behaviours are voluntary or self-determined [12,13]. In this sense, motivational behaviour can be fragmented into three types of motivation [14]: autonomous motivation, controlled motivation and amotivation, each determined by different forms of motivational regulation ranging from the highest to the lowest level of regulation. In autonomous motivation, behaviours are given by integrated regulation (the activity is assimilated within the self), identified regulation (achieve an action in line with the person’s values) and intrinsic regulation (performing an activity for its enjoyment or because it is challenging). In controlled motivation, behaviours are assessed by external (execute an action to get a reward or avert chastisement) and introjected (performing an activity to feel good and avoid feelings of guilt or anxiety) regulation. Finally, at the opposite extreme of motivation is amotivation, which is the absence and lack of interest and motivation.

SDT defends the existence of three basic psychological needs (BPN) that can be supported or thwarted by the social environment: autonomy, competence, and relatedness needs [15]. In the educational context, the physical education (PE) teacher can be crucial in supporting or thwarting these three needs [16,17,18]. The teaching behaviours concerning out-of-school activities during PE classes can encourage their students’ practice of extracurricular PA, supporting their autonomy, competence, and relatedness [19,20]. Specifically, PE teachers’ autonomy support to extracurricular PA implies using strategies to encourage students’ initiative, and provide choices, options, and opportunities to do active sports and/or exercise in their free time. Concerning extracurricular PA, competence-supportive PE teachers offer their students challenging extracurricular activities, show confidence in their capacity to effectively engage in these types of PA, express clear expectations and provide activities adjusted to the students’ skill levels, helping them to achieve their goals and giving positive feedback when they perform active sports and/or exercise in their free time. Finally, relatedness-supportive PE teachers express affection to their students when they share their experiences about their leisure-time PA, they propose out-of-school activities with peers, and they dedicate time and energy to listening to their students and helping them feel socially connected [15,18,19,20]. In this sense, PA and fitness are related to different types of changes in the brain relevant to cognitive function and learning [21,22,23,24].

Previous studies have shown how a need-supportive interpersonal style is a predictor of a more self-determined motivation, which in turn, can predict the intention to be physically active [16], knowledge [17], engagement [18], and performance in PE [18]. Furthermore, it is essential to understand that the activities teachers develop in their classrooms can affect students’ extracurricular lives. For example, authors such as Tilga et al. [25], Tilga et al. [26] and Hagger et al. [19] have found that students who perceive that their PE teacher supports autonomy show higher levels of autonomous motivation for PA and greater intention to perform PA in their free time. Therefore, it can be concluded that extracurricular PA-supportive PE teachers can impact students’ out-of-school behaviours, positively impacting the quality of motivation and intentions to engage in PA and PA levels [27]. Based on previous studies, one of the main limitations of school-based interventions is their low sustainability once the research team stops implementing the intervention. Although there are several reasons that may cause this abandonment of implementation, lack of teacher training is one of the main reasons. Therefore, previous literature suggests that training and involving teachers in the intervention programme could positively contribute to the sustainability of the school-based intervention [28].

### 1.2. Previous Intervention Studies Based on SDT in the School Context

Previous systematic reviews and meta-analyses on SDT-based school interventions have shown that teachers who support students’ motivational processes generate adaptive consequences towards PA [29,30], but the effect of these interventions is low [8]. In this sense, previous studies have implemented motivational strategies or used a multicomponent theoretical design (i.e., intervening from different perspectives, areas, or actors), combining different approaches with SDT to obtain positive effects on PA behaviour [8,31,32,33,34,35]. Concerning SDT, Kelso collected thirty studies using this theory as a theoretical framework [8]. However, analysing these researches in detail, only two studies—Moreno-Murcia and Sánchez-Latorre [36] and Kokkonen et al. [32]—developed a training programme with PE teachers, measuring the out-of-school outcomes; that is, students’ motivation for leisure-time PA and their out-of-school PA levels. Moreover, only Moreno-Murcia and Sánchez-Latorre [36] found significant differences in intrinsic motivation and PA levels after the intervention. Thus, the results should be interpreted with caution. Given that the evidence of out-of-school programmes is limited, more research is needed to identify the most appropriate strategies to elicit more self-determined forms of motivation and increase students’ out-of-school levels of PA.

### 1.3. The Present Study

In accordance with the previous studies and the theoretical framework of SDT, we highlighted that: (a) most of the studies were based on different theories; (b) they assessed only variables within PE; (c) they were applied to young people over 12 years of age; (d) PE teachers were not always involved in the intervention; and (e) most of the strategies developed only focused on autonomy support. Therefore, this study aims for the PE teacher to apply a series of SDT-based motivational strategies that support autonomy, competence, and relatedness towards PA in primary education students to improve their motivation for PA and, consequently, their extracurricular PA. For this purpose, an intervention will be carried out in students (10 to 12 years), where strategies will be applied to support the three BPNs (i.e., autonomy, competence, and relatedness) concerning PA and with the teachers playing a more active role, as they will co-create and develop these motivational strategies to promote motivation and out-of-the-school practice of PA.

## 2. Methods

### 2.1. Design and Participants

This quasi-experimental study will be carried out in Cáceres (Extremadura, Spain). Convenience sampling will be conducted in six different Primary Schools. Three schools will be randomly assigned to the control school and the other three schools to the experimental school. The sample size will be estimated using the following formula: *n* = (Z)^2^ (*p*(1 − *p*) e^2^), where “*n*” is the sample size, Z = 1.96 (95% confidence interval), *p* = number of 4th and 5th primary school students in the city where the study will be conducted (±3350 students), and e = margin of error (3%). The minimum sample size (considering a 10% non-response) will be 345 students. All the schools will have similar socio-demographic and built-environment characteristics [37]. School courses in Extremadura run from early September to mid-June, with a Christmas break from late December to early January and a break around March or April for the Easter holidays. As seen in Figure 1, assessments will be completed at baseline at the beginning of the school course (Term 1, February) and after the intervention (Term 2, June). A follow-up measurement will be conducted at the beginning of the following school course (Term 3, October). The study has been agreed upon by the Ethics Committee of the University of Extremadura (120/2018) and follows the guidelines of the Declaration of Helsinki.

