#### 2.1.1. Selection Process and School Characteristics

A roster of the primary schools in the city of Cáceres will be drawn up. This list will be categorised according to the nature (public or private) of the potential participating schools, resulting in 26 schools. Subsequently, an explanatory letter with the project’s objectives will be sent to the principals, who will be asked to reply to the e-mail if they decide to participate to receive a more detailed explanation of the project. Schools will have a maximum of 15 days to confirm their participation. As the project will be conducted in PE lessons, the PE teachers must support the principals.

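### The minimum of 345 pupils cannot be reproduced from its labelled inputs, and the formula behind it does not size a comparison of three schools with three

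*Protocol article*

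**What the plan says.** The only sample-size justification is in section 2.1 (Design and Participants) of the protocol article. It introduces the calculation with "The sample size will be estimated using the following formula: *n* = (Z)^2^ (*p*(1 − *p*) e^2", sets Z at 1.96 for 95% confidence, and defines p as the "number of 4th and 5th primary school students in the city where the study will be conducted (±3350 students"). It then closes: "and e = margin of error (3%). The minimum sample size (considering a 10% non-response) will be 345 students".

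No expected proportion is stated. Nor are a finite-population correction, an effect size, an SD, a power or an intraclass correlation (ICC).

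The same section describes convenience sampling of six schools, with three assigned at random to each arm. Section 2.4 makes change in motivation for out-of-school physical activity the primary outcome, with significance at 0.05. Section 1.2 says of earlier school programmes of this kind, "but the effect of these interventions is low".

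**The concern.** There are two separate problems.

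- **The number.** The symbol p in this formula must be a proportion between 0 and 1, but the article defines it as a count of pupils. A reader who substitutes the labelled inputs cannot arrive at 345. The stated margin and the stated non-response allowance therefore cannot be checked against the figure they are said to produce.
- **The question answered.** The formula gives the half-width of a confidence interval for one proportion in a simple random sample. The study compares change in a motivation score between two arms of three schools each. A correct version of the formula would still say nothing about whether that comparison can detect a plausible effect.

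At stake is how the result will be read. If 345 is taken as adequate for the primary comparison, a null result may be misread as evidence of no effect, in a field where the article itself calls effects low.

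**Working it through.** **Inputs from section 2.1:** Z = 1.96; head count 3350; e = 0.03; non-response 10%; six schools, three per arm; stated result 345.

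**Assumptions, not in the article:** p = 0.5 where marked; ICC 0.01, 0.02 and 0.05; 80% power; equal school sizes.

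**1. The formula as labelled.** With p = 3350, p(1 − p) = 3350 × (−3349) = −11,219,150. Multiplying by e², as the text shows: 1.96² × (−11,219,150) × 0.03² ≈ −38,790. Dividing by e² instead: about −4.8 × 10¹⁰. Both are impossible, so restoring a division sign does not rescue the formula.

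**2. The usual formula for these inputs.** Let N = 3350 be the population and p a proportion:

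n = N Z² p(1 − p) / [e² (N − 1) + Z² p(1 − p)]

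With p = 0.5 (assumed) and e = 3%: Z² p(1 − p) = 0.9604, so n = 3350 × 0.9604 / (0.0009 × 3349 + 0.9604) = 3217.34 / 3.9745 = 809.5, that is 810. With 10% non-response: 809.5 / 0.9 = 899.4, that is 900. Without the finite-population correction the figures are 1068 and 1186. None is near 345.

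**3. Which inputs do give 345?**

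| e | p | n before non-response | n after 10% non-response |
|---|---|---|---|
| 5% | 0.5 | 344.7 → 345 | 383.03 → 384 |
| 3% | 0.10 | 344.7 → 345 | 383.03 → 384 |
| 3% | about 0.088 | about 311 | about 345 |

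The first two rows agree exactly because 0.25 / 0.05² = 0.09 / 0.03² = 100. The second uses every number in the text, but with the 10% acting as the expected proportion. The third includes the allowance, but needs a proportion stated nowhere. A fourth route, e = 5% with the allowance, needs an unstated p of about 0.335.

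**4. The two-arm comparison (illustration).** With 345 pupils in six schools, m = 345 / 6 = 57.5 per school. For independent pupils the difference detectable with 80% power at two-sided 5% is 2.80 × √(4/345) = 0.30 SD.

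With schools as the unit there are 6 − 2 = 4 degrees of freedom, and the noncentrality needed for 80% power is 3.761. In SD units, with no gain from baseline adjustment:

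detectable difference = 3.761 × √{2 [ICC + (1 − ICC)/57.5] / 3}

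| Assumed ICC | ICC + (1 − ICC)/57.5 | Detectable, 4 df | Detectable, large-sample multiplier 2.80 |
|---|---|---|---|
| 0.01 | 0.0272 | 0.51 SD | 0.38 SD |
| 0.02 | 0.0370 | 0.59 SD | 0.44 SD |
| 0.05 | 0.0665 | 0.79 SD | 0.59 SD |

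The last column allows for clustering but not for having only six schools. Every entry exceeds 0.30 SD.

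**The case against.** - **Cause of the discrepancy.** A reader might infer that 345 is simply the 5%-margin figure, that the true margin is 5.0%, and that e should be restated as 5%. The article does not support this. At n = 345 the margin is 5.0% only if p = 0.5; at p = 0.10 it is 3.0%. Restating e as 5% could replace a correct input with a wrong one. Nor can it be proved that the allowance was left out, since a p near 0.088 would include it. This part of the objection stands in full.
- **The missing division.** Multiplication by e² may be a fraction bar or slash lost when the text was extracted, so the −38,790 carries little weight. That stands. The definition of p is in words, however, and is no extraction artefact.
- **Detectable differences.** The ICCs are assumed, the article gives no size for a low effect, and the outcome is change, so correlation with baseline could reduce these values. That stands: the figures are illustrative and do not show that the study is underpowered.
- **Limited consequence.** The 345 is a minimum, all 4th- and 5th-graders in the participating schools are invited (section 2.1.3), and the article claims no power. This limits the practical harm. It does not make the justification correct, or relevant to the primary comparison.
- **Condensed article.** Detail may be left to a fuller document. But the article chose to print a formula, inputs and a result, and these do not agree.

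**Conclusion.** The point holds in two parts. First, 345 cannot be obtained from the inputs as labelled. The definition of p makes the formula invalid, and under the conventional p = 0.5 the stated 3% margin needs 810 responders, or 900 allowing for 10% non-response. On every reading examined, at least one input is mislabelled, missing or unused. Which one is not determinable from the article.

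Second, even when corrected, this is a precision calculation for a single proportion under simple random sampling. It does not justify a comparison of change in motivation between three and three schools. The first part rests on arithmetic, with p = 0.5 as the only added assumption for the 810 and 900. The 0.51 to 0.79 SD range rests on the assumed ICCs, equal school sizes, 4 degrees of freedom and no baseline adjustment.

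**What to change.** 1. Print n = N Z² p(1 − p) / [e² (N − 1) + Z² p(1 − p)], with N = 3350 and p defined separately as a proportion.
2. State the p and e actually used, and whether the 10% is non-response or the expected proportion.
3. Restate the figure to match. For either exact route (5% with p = 0.5, or 3% with p = 0.10), this is 345 responders and, with 10% non-response, 384 to invite. If 3% with p = 0.5 is meant, it is 810 and 900.
4. State that this is a precision figure and not a power calculation. Report the difference in the primary motivation score that six schools can detect over an assumed ICC range, with the degrees of freedom and any baseline adjustment made explicit.

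The cost is wording only, though the stated precision may become less favourable. If the city's pupils were spread evenly over the listed schools ("resulting in 26 schools"), six schools would hold about 3350 / 26 × 6 = 773 eligible pupils. That covers 384 invitations but not 810 responders, so under the last reading in step 3 the claimed margin would have to be relaxed for six schools of that size.

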### 2.4. Statistical Analysis

The primary outcome will be changes in the levels of students’ motivation for out-of-school PA. Secondarily, perceived exercise autonomy support, the intention to be physically active, perception of PA levels, engagement in PE and academic performance will also be assessed. For this purpose, firstly, the nature of the variables will be taken into account through the application of normality, validity, and reliability tests. Secondly, the principles of independence, normality, linearity and variance of the study variables will be tested for general linear model analyses. Thirdly, intergroup and intragroup differences will be analysed with repeated-measures ANOVA or nonparametric tests such as McNemar’s or the Kruskall–Wallis tests, as appropriate. For continuous variables, Bonferroni-corrected multiple paired *t*-tests will be calculated to determine intra-group (i.e., between the experimental and control group) and inter-group (i.e., between the pre-test and post-test) differences. For categorical variables, a chi-square test will be performed. While Cramer’s V will be used to describe the degree of association between categorical variables and experimental and control schools, McNemar’s test will be used to analyse baseline and post-intervention differences in categorical variables in experimental and control schools, respectively. Effect sizes will be assessed using Partial Eta Squared (η_p_^2^) and Cramer’s V values for continuous and categorical variables, respectively. Effect sizes will be considered small, moderate or large when η_p_^2^ is greater than 0.01, 0.06 and 0.14, respectively, and when Cramer’s V is greater than 0.10, 0.30 and 0.50, respectively. Significance will be set at *p* < 0.05 for all analyses.

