## 4. Conclusions

It is expected that these school-based interventions aimed to promote the PA practice in the leisure time of students’ primary school will have positive consequences on them, such as increasing the levels of intrinsic motivation, increasing engagement during PE classes, reducing controlled motivation and demotivation towards PE and towards the practice of PA, and, consequently, there will be a positive predisposition towards the intention to carry out PA and increase the levels of PA practice of the students.

Regarding the first limitation that we can find in the development of the intervention, the need to have a supervisor in order to control the compliance and development of the strategies developed by the teachers may be a factor that may hinder the replication of similar interventions. Therefore, researchers who wish to carry out a similar intervention are urged to take into account the need or not to include an agent who can supervise the intervention to be carried out.

On the other hand, another of the limitations that can be found is due to the possible curricular modifications that the intervention may undergo as a result of the continuous legislative modifications in the educational context. Furthermore, it is important to highlight that each school has a different educational reality (i.e., the different organisation of the centre, practice spaces, quantity of PE teachers and students), and therefore, the strategies to be developed must be adapted and can be developed differently in the schools of the intervention programme.

Finally, taking into account the educational reality of PE teachers, it is important to emphasise that the teachers in this research have the theoretical and practical support of a research team. For this reason, it is encouraged to encourage PE teachers that if they do not have similar support behind them, they should carry out autonomous learning and training in motivational theories such as SDT in order to improve the teaching-learning process of their students.

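### School similarity is asserted, but no described selection criterion secures it, and the plain 3 v 3 allocation makes no stated use of the public/private category already recorded

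*Protocol article*

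**What the plan says.** Section 2.1 (Design and Participants) describes the sampling as follows: "Convenience sampling will be conducted in six different Primary Schools". On allocation it says: "Three schools will be randomly assigned to the control school and the other three schools to the experimental school". It then states, with a citation, that "All the schools will have similar socio-demographic and built-environment characteristics". The sentence looks forward, to schools not yet recruited.

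Section 2.1.1 (Selection Process and School Characteristics) describes a roster of the city's primary schools: "This list will be categorised according to the nature (public or private) of the potential participating schools, resulting in 26 schools". A letter goes to the principals, "who will be asked to reply to the e-mail if they decide to participate" and so receive a fuller explanation; schools then have up to 15 days to confirm. The section gives no similarity criterion, no quota by school type and no rule for choosing six if more confirm. It does not say what the public/private category is for.

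Section 2.4 (Statistical Analysis) makes change in motivation for out-of-school physical activity the primary outcome and says that "intergroup and intragroup differences will be analysed with repeated-measures ANOVA or nonparametric tests". It names no school-level term. Section 4 (Conclusions) observes that "it is important to highlight that each school has a different educational reality", and gives as examples the organisation of the centre, practice spaces, and the numbers of PE teachers and students.

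**The concern.** The similarity sentence reads as reassurance that the two sets of schools are comparable, but nothing in the described recruitment produces it. Volunteers from a mixed list need not resemble one another, and the article's own limitations paragraph lists ways in which schools differ. Practice space in particular bears on the built environment that Section 2.1 says is similar.

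With three schools per arm, random assignment gives little protection against an uneven split of a school-level factor. Public or private status is recorded before allocation, so it could be balanced at almost no cost. If it falls unevenly and motivation or activity changes differently over the school year in the two types of school, part of that difference would appear as a programme effect, or would mask one. More pupils per school would not help. With six schools there is also little room for a later analysis to separate type from arm.

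**Working it through.** **Inputs.** Six schools and a 3 v 3 random assignment (Section 2.1). A source list of 26 schools, categorised as public or private, with the split not given (Section 2.1.1). The number of private schools among the six, *k*, is not stated, so every value is shown. The article gives no figure for balance between arms, so there is nothing of its own to reproduce; its minimum sample of 345 students plays no part here.

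**Formula.** There are C(6,3) = 20 equally likely allocations. The probability that *x* of the *k* private schools fall in a given arm is C(k,x) × C(6−k,3−x) / 20.

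**Calculation.**
- *k* = 2: both in a given arm, C(2,2) × C(4,1) = 4 allocations; for either arm, 8/20 = 40%. Even split: C(2,1) × C(4,2) = 12, or 60%.
- *k* = 4: the same counts with the types exchanged, so 8/20 = 40% for a 3 v 1 split of private schools and 12/20 for 2 v 2.
- *k* = 3: all three in a given arm, C(3,3) × C(3,0) = 1 allocation; for either arm, 2/20 = 10%. The other 18 of 20 are 2 v 1 splits.
- *k* = 1 or 5: the arms always differ by exactly one school.
- *k* = 0 or 6: no difference is possible.

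| Private schools among the six | Chance that arms differ by 2 or more, plain 3 v 3 | Same, restricted to the most balanced splits | Splits remaining |
|---|---|---|---|
| 0 or 6 | 0% | 0% | 20 of 20 |
| 1 or 5 | 0% | 0% | 20 of 20 |
| 2 or 4 | 40% | 0% | 12 of 20 |
| 3 | 10% | 0% | 18 of 20 |

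**Averaging over the unknown mix.** Suppose that the six were a random draw from the 26 and that between 4 and 13 of the 26 were private. Neither is stated; both are assumptions. The chance of a difference of two or more schools is then 8% (4 private) to 23% (13 private).

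**What the splits mean.** When *k* = 2 and both private schools land in one arm, that arm still holds one public school and the other arm holds three. Type is imbalanced but varies within an arm. Only the 3 v 0 split at *k* = 3 makes type and arm the same variable.

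**Text against text.** Section 2.1 asserts similarity; Section 2.1.1, where a criterion would be expected, gives none; Section 4 lists differences between schools.

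**The case against.** Several parts of the opposing case stand.

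- A reader might infer that the public/private category is recorded and then ignored. The article does not say so. It is silent on the purpose, and a fuller protocol may use the category for invitation, selection or stratified allocation. What can be said is that no use is stated.
- A reader might also infer that the six schools will be mixed, or that a serious imbalance is likely. The article does not give the mix, and volunteers could all be of one type. The 40% is the worst case over *k*, not an expected value.
- It is tempting to say that type would be inseparable from the programme effect. That is true only of the 3 v 0 split. The 40% figure belongs to a lesser imbalance.
- The primary outcome is change, measured from baseline. Stable differences in level between school types largely drop out of a comparison of change between groups; bias needs change itself to differ by type. The article does not show that it does. Family affluence is also measured on each pupil (Section 2.3), although Section 2.4 names no adjustment for it.
- Chance imbalance after random allocation is not in itself an error, and similarity might be screened for after schools confirm.

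None of this supplies the missing criterion. The cited reference cannot by itself secure the similarity of schools that have yet to volunteer, and the described process does not do so either. Nor can balance at allocation be restored by a later analysis plan once six schools have been assigned.

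**Conclusion.** The point holds in a limited form. The similarity statement in Section 2.1 is not supported by the selection described in Section 2.1.1 and sits uneasily with Section 4. The allocation as described leaves a 40% chance of a two-school difference in type if 2 or 4 of the six are private, a 10% chance of complete separation if 3 are, and no chance of a difference of two or more otherwise. These figures assume that the 20 splits are equally likely, as the plain wording implies. An imbalance short of 3 v 0 matters only if change differs by school type, which is plausible but not shown. The document does not establish that the trial will be confounded or that the category is discarded.

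**What to change.** In Section 2.1, replace the similarity assertion with the criterion actually applied to schools and say at what step it is applied. State whether public/private status is used in selection or allocation. If both types enter, list the 3 v 3 splits that balance type as evenly as possible and draw one of them at random, once. Report school type by arm with the baseline data.

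The cost is a few sentences and one constrained draw. The admissible allocations fall from 20 to 12 (2 or 4 private) or 18 (3 private). A one-school difference cannot be removed when the number of private schools is odd, and with six schools only one or two factors can be balanced in this way.
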